### Data management {19}

Participant data will be recorded on case report forms (CRF). Separate CRFs will be used to collect clinical information and patient reported information.

To ensure high-quality data, the CRFs will be processed at YTU, using a licensed, automated, electronic system which allows data to be entered, checked and validated. A study-specific data management plan will document further details regarding the specifics of processing of this data.

Study documentation will be archived and retained in accordance with Good Research Practice and UK Law for 5 years after study completion in the Trial Master and Investigator Site Files, after which time this information will be securely destroyed.

### Confidentiality {27}

To maintain confidentiality participants will be assigned a unique four-digit number (study ID) which will be used to identify them throughout the trial. All data for the trial will be stored and handled according to relevant data protection principles and regulations.

Participant identifiable information will be stored on a secure data management system accessible only by trial staff via individual passwords. Where participant identifiable data is held in a printed format, it will be held separate from participant CRFs and kept in locked filing cabinets accessible only to the research team.

### Plans for collection, laboratory evaluation and storage of biological specimens for genetic or molecular analysis in this trial/future use {33}

Not applicable. There is no collection of biological specimens in the PROFHER-2 trial.

## Statistical methods

### Statistical methods for primary and secondary outcomes {20a}

All analyses will be undertaken using the principle of intention-to-treat, where participants are analysed as randomised, regardless of what treatment they received. Analysis will be undertaken using Stata v17 (or later), and models will be assessed at a 5% significance level, unless otherwise stated. All analyses will be preplanned and detailed in a statistical analysis plan, which will be approved by the trial oversight committees prior to analysis.

### Primary analyses

The primary outcome is the OSS at 24-month post-randomisation. The difference in OSS at 24 months will be compared between the arms of the trials using mixed effects models. The model will adjust for a dummy variable for the change in allocation ratio and relevant baseline characteristics, including pre-fracture OSS, baseline grip strength, and presence of an associated dislocation (if applicable), as well as OSS at interim follow-ups, with correlation within each participant over time modelled by an appropriate covariance structure. The treating surgeon will be included as a random effect; if clusters are too small, the centre will be included instead.

Two separate models will be used. The first model will compare the two surgical arms and include all participants randomised to either of these arms. The second model will compare the surgical and non-surgical arms but will only include participants who were eligible to receive NS as an allocation (i.e., excluding anyone with a dislocation that required general anaesthesia for reduction) and will be run once for the RSA v NS comparison, and then run separately for the HA v NS comparison. Both models will follow the principle of intention-to-treat except for a pre-specified complier average causal effect (CACE) analysis of the primary outcome.

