## Data collection and management

### Plans for assessment and collection of outcomes {18a}

Data will be collected at baseline and 6, 12, and 24 months via either paper questionnaire or telephone. The data collection timetable is outlined in Appendix 2.

At baseline, the OSS and EQ-5D-5L will be collected with both an assessment of pre-injury and post-injury scores. PROMIS and pain VAS will also be collected. Epidemiological data will be collected including patient demographics, comorbidities, prior injury to the affected arm, and smoking status. Details of surgical and medical care provided will be recorded.

Data regarding any physiotherapy provided will be collected until discharge from physiotherapy. This will include the number and length of sessions, care provided, and range of motion at discharge.

In addition, at 6 months participants will have an X-ray and assessment of range of motion.

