### Secondary analyses

The secondary outcomes (pain, range of motion, estimates of OSS at 6 and 12 months) will be analysed in a similar way to the primary, using appropriate models and adjusting for the same covariates as the primary models.

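### The primary-model sentence lists OSS at 6 and 12 months among the adjustment variables while also treating them as repeated outcomes; their role must be stated

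*Protocol article*

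**What the plan says.** Under Primary analyses the Protocol article fixes the endpoint ("The primary outcome is the OSS at 24-month post-randomisation") and the method ("The difference in OSS at 24 months will be compared between the arms of the trials using mixed effects models"). The next sentence gives the adjustment set: "The model will adjust for a dummy variable for the change in allocation ratio and relevant baseline characteristics, including pre-fracture OSS, baseline grip strength". It then adds associated dislocation where applicable and goes on "as well as OSS at interim follow-ups, with correlation within each participant over time modelled by an appropriate covariance structure". One verb governs the whole list. The same paragraph serves RSA v HA, RSA v NS and HA v NS.

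Item {18a}, on how outcomes are assessed, identifies the interim follow-ups: "Data will be collected at baseline and 6, 12, and 24 months via either paper questionnaire or telephone". Interim OSS therefore means the 6- and 12-month scores.

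Under Secondary analyses, OSS at 6 and 12 months is itself to be estimated, in a manner similar to the primary analysis and "adjusting for the same covariates as the primary models".

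**The concern.** The 6- and 12-month scores are outcomes that treatment can change. As covariates they would turn the arm coefficient into the 24-month difference between participants with equal earlier scores. That is not the total 24-month difference named in the objectives and used in the sample size. It also gives up the protection of randomisation, because arms matched on a post-treatment score need not be matched on prognosis.

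Two further passages depend on the same wording. Read literally, the secondary rule would adjust the 6- and 12-month OSS for themselves. And the sensitivity analysis under {20c}, which imputes missing covariates of the primary model, would or would not cover interim OSS according to which role it has.

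Two analysts could follow the sentence, fit different models and report different primary results. The article also says that the statisticians analysing the data will not be blinded, so the choice should be settled in writing before analysis.

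**Working it through.** **1. The two halves of the sentence.** If 24-month OSS is the only response, each participant contributes one value, and there is no within-participant correlation over time to model. The covariance clause needs several responses per participant. The adjustment list, by contrast, puts interim OSS on the covariate side. Both cannot describe the same role.

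**2. The plan's own sample size.** Inputs from Sample size {14}: 5 points (RSA v HA), 6 points (each surgical arm v NS), SD 12, 90% power, two-sided 5%, 320 evaluable, 15% attrition, 380 recruited. At 2:2:1, 320 splits 128:128:64.

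- NS arm: (1.96 + 1.2816)² × 144/36 × (1 + 1/2) = 63.04, so 64; 5 × 64 = 320.
- RSA v HA: SE = 12√(2/128) = 1.5; 5/1.5 − 1.96 = 1.37; power 0.915.
- Surgical arm v NS: SE = 12√(1/128 + 1/64) = 1.84; 6/1.84 − 1.96 = 1.31; power 0.904.
- Attrition: 320/0.85 = 377, against 380 stated.

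The figure reproduces, and it rests on the total 24-month difference.

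**3. What the literal model would estimate.** Let d6, d12 and d24 be the arm differences, and b6 and b12 the within-arm regression coefficients of 24-month OSS on the two interim scores. The arm coefficient becomes d24 − b6·d6 − b12·d12. The protocol gives neither the correlations nor d6 and d12, so these are assumptions. I take SD 12 at every visit, complete data and no variance reduction from baseline covariates.

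With equal correlation ρ, b6 = b12 = ρ/(1 + ρ), and the residual SD is 12√(1 − 2ρ²/(1 + ρ)). If the effect is also constant over time, the share left is (1 − ρ)/(1 + ρ):

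| ρ | Left of 5 points | Power, 128 v 128 | Left of 6 points | Power, 128 v 64 |
|---|---|---|---|---|
| 0.3 | 2.69 (54%) | 0.49 | 3.23 | 0.47 |
| 0.5 | 1.67 (33%) | 0.27 | 2.00 | 0.27 |
| 0.7 | 0.88 (18%) | 0.15 | 1.06 | 0.14 |

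Example at ρ = 0.5: 5 × 0.5/1.5 = 1.67; residual SD 12√0.667 = 9.80; SE 9.80 × 0.125 = 1.22; 1.67/1.22 − 1.96 = −0.60; power 0.27. More than half is lost only when ρ exceeds 1/3.

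**4. Other assumptions, true 24-month effect 5 points.**

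| Effect at 6, 12, 24 months | Correlation | Share lost |
|---|---|---|
| 5, 5, 5 | decaying, ρ per 6 months of 0.5 / 0.7 / 0.8 | 25% / 49% / 64% |
| 1.25, 2.5, 5 | equal, 0.5 / 0.7 | 25% / 31% |
| 0, 0, 5 | any | 0% |
| 8, 6.5, 5 | equal, 0.5 | 97% |
| 8, 6.5, 5 | equal, 0.6 and above | over 100%: sign reverses |

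Under decaying correlation the 12-month coefficient is ρ² and the 6-month coefficient is zero, so the share lost is ρ². In the last two rows the arm coefficient is 5 − 14.5·ρ/(1 + ρ), which is 0.17 at ρ = 0.5 and −0.44 at 0.6.

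Power need not fall with the estimate. For the effect growing in proportion to time, power is 0.86 and 0.94 at ρ of 0.5 and 0.7, although the estimate is only 3.75 and 3.46 points.

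**5. Simulation check.** In 400 simulated trials of 128 per arm (constant effect, equal correlation 0.3, 0.5, 0.7), interim OSS as covariates gave mean estimates of 2.67, 1.68 and 0.78. The 24-month contrast with interim OSS as outcomes gave 4.94, 4.93 and 4.86. With complete data, that contrast from an unstructured repeated-measures model is the difference in 24-month means, and it was computed that way.

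**The case against.** The strongest reply is that the sentence resolves itself. The covariance clause has no meaning with a single response, and 6- and 12-month estimates are the natural output of a repeated-measures model. Nobody would adjust 6-month OSS for itself, so the covariates carried over to the secondary analyses must be the baseline ones. Full specification is deferred to a statistical analysis plan that the oversight committees approve before analysis, and that plan is not among the documents at hand.

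Most of this stands. Repeated measures is the likelier intent, and the secondary rule is better seen as evidence for that intent than as a second error. The absence of time and arm-by-time terms from an article is no fault. What does not stand is that the matter is merely deferred: the article states what the primary model adjusts for, and the statement is wrong as worded.

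A reader might infer that the planned analysis removes most of the 24-month effect. The documents do not support that. They do not show that the literal model will be fitted, and they give no correlation or trajectory from which a loss could be computed. A reader might also infer that participants missing an interim score would simply be lost. That too needs the literal reading, and {20c} plans a repeat analysis with missing covariates imputed, although only as a sensitivity analysis.

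**Conclusion.** The primary-model sentence is misstated and conflicts with itself. It places post-randomisation outcomes in the adjustment list while describing a model in which they are responses. This affects all three comparisons. It is a defect of specification, not a shown loss of effect.

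If the literal model were fitted, the target would no longer be the total 24-month difference. The loss could be anything from none (effect only after 12 months) to more than the whole effect (larger early effect, equal correlation of 0.6 or more). The fall from 0.915 to about 0.49, 0.27 or 0.15 holds only for a constant 5-point effect with equal correlation of 0.3, 0.5 or 0.7. The power figures use the original 2:2:1 split of 320. The width of the range is itself the reason to remove the ambiguity.

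**What to change.** In Primary analyses, and in the statistical analysis plan if it carries the same wording, state that:

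- OSS at 6, 12 and 24 months are the repeated outcomes;
- the fixed effects are arm, time, arm-by-time, the allocation-ratio dummy and the baseline covariates already listed (pre-fracture OSS, grip strength, associated dislocation where applicable);
- the primary estimate is the arm contrast at 24 months.

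In Secondary analyses, state that the shared covariates are the allocation-ratio dummy and the baseline covariates only, with no post-randomisation measure among them.

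The dislocation covariate should stay. A separate randomisation-sequence term should not be added: the NS models draw only on the 2:2:1 and 1:1:1 sequences, so it would duplicate the allocation-ratio dummy there.

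The cost is a sentence or two in each section, made before analysis. No data collection or sample size changes. If repeated measures was always intended, the analysis does not change either.

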### Secondary analyses

The secondary outcomes (pain, range of motion, estimates of OSS at 6 and 12 months) will be analysed in a similar way to the primary, using appropriate models and adjusting for the same covariates as the primary models.

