### Outcomes {12}

The primary outcome is the OSS at 24 months. The OSS provides a total score based on the person’s subjective assessment of pain and activities of daily living, has established content validity in post-operative patients [23], and has been used successfully in other large surgical trials of shoulder disorders [8, 24–26]. This outcome measure has also been chosen to allow comparison with the data obtained from the PROFHER trial [8].

Secondary outcomes will include:Quality of life using EQ-5D-5L [27]Pain using the Patient-Reported Outcomes Measurement Information System (PROMIS) pain interference measure [28]Pain using a visual analogue pain scale (from no pain to worst imaginable pain – using a 10 cm line)Range of shoulder motion (recorded at discharge from physiotherapy and independently assessed at 6 months post-randomisation i.e., not by the treating surgeon)Healing and implant position using AP and axillary (and scapular Y view if available) X-rays taken at 6 months post-surgeryFurther procedures and complications.

In addition, grip strength on the uninjured side will be collected at baseline using a Jamar Dynamometer [29]. This will be used to assess frailty and as a predictor of morbidity and mortality. Physiotherapy utilisation will also be collected during the trial using case report forms specifically developed for the study.

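### As worded, the secondary analyses do not adjust pain VAS and PROMIS for their own baseline values, although both are collected at baseline

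*Protocol article*

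**What the plan says.** The Secondary analyses section of the protocol article covers the secondary outcomes in one sentence. It states that "The secondary outcomes (pain, range of motion, estimates of OSS at 6 and 12 months) will be analysed in a similar way to the primary", and it continues by calling for appropriate models and "adjusting for the same covariates as the primary models".

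The covariates referred to are in the Primary analyses section: "The model will adjust for a dummy variable for the change in allocation ratio and relevant baseline characteristics". The baseline characteristics named there are "relevant baseline characteristics, including pre-fracture OSS, baseline grip strength, and presence of an associated dislocation". The same sentence brings in OSS at the interim follow-ups, with within-participant correlation modelled.

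Pain is measured by two secondary outcomes in the Outcomes section: a 10 cm visual analogue scale and the "Patient-Reported Outcomes Measurement Information System (PROMIS) pain interference measure". On baseline data, the section on plans for assessment says that "PROMIS and pain VAS will also be collected". The schedule in Appendix 2 marks both scales at baseline and at 6, 12 and 24 months.

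**The concern.** When an outcome is measured both before and after randomisation, its own baseline value is usually the first covariate to consider. The primary model follows this logic in part, since the OSS outcome is adjusted for an OSS baseline. The secondary sentence carries over the same covariates instead of the same logic. A pain model written from it would contain pre-fracture OSS, which is a different scale referring to the time before the injury, and would leave out the baseline pain score that the trial collects.

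Two things are at stake, both modest. Any part of the outcome variance that baseline pain explains beyond the named covariates stays in the error term. And if the arms happen to differ in baseline pain, the estimate is not corrected for it. This matters most in the comparisons with non-surgical treatment, which leave out participants whose dislocation needed general anaesthesia for reduction and are therefore the smaller ones. Pain is part of objective iii.

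**Working it through.** **1. The plan's own figure, for context.** The sample size rests on the OSS: SD 12, 90% power, two-sided 5%, differences of 5 points (RSA v HA) and 6 points (surgery v NS), under the initial 2:2:1 ratio. By the normal approximation:

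- RSA v HA: n per arm = 2 × (1.960 + 1.282)² × 12² / 5² ≈ 121.04, so 122.
- Surgery v NS at 2:1: n in NS = (1 + 1/2) × (1.960 + 1.282)² × 12² / 6² ≈ 63.04, so 64, with 128 in each surgical arm.
- Total: 128 + 128 + 64 = 320, as stated. With 15% attrition, 320 / 0.85 ≈ 377, against the stated target of 380.

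No pain outcome enters this calculation, so the present point does not touch it.

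**2. The passages side by side.**

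| Outcome in the secondary sentence | Own baseline in the schedule? | Own baseline among the named covariates? |
|---|---|---|
| Pain VAS | Yes | No |
| PROMIS pain interference | Yes | No |
| Range of motion | No (6 months only) | Not applicable |
| OSS at 6 and 12 months | Yes | Yes, as pre-fracture OSS |

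The gap is confined to the first two rows. Nowhere does the article say that a secondary outcome is adjusted for its own baseline.

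**3. Size.** Let r be the partial correlation between baseline and follow-up pain, given the covariates already in the model. The documents give no value, so r is an assumption, shown here from 0.1 to 0.4.

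- Residual variance after adding the baseline, relative to before: 1 − r².
- Equivalent increase in participants: 1 / (1 − r²) − 1.
- Reduction in standard error: 1 − √(1 − r²).

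| r (assumed) | Variance ratio | Variance reduction forgone | Equivalent extra participants | Standard error reduction |
|---|---|---|---|---|
| 0.1 | 0.99 | 1% | 1% | 0.5% |
| 0.2 | 0.96 | 4% | 4% | 2.0% |
| 0.3 | 0.91 | 9% | 10% | 4.6% |
| 0.4 | 0.84 | 16% | 19% | 8.3% |

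The low end deserves weight. The section on plans for assessment records pre-injury and post-injury versions of the OSS and EQ-5D-5L, but mentions no pre-injury version of VAS or PROMIS. Baseline pain therefore appears to be pain shortly after an acute fracture, which may predict pain at 6 to 24 months only weakly.

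**The case against.** The best defence is that the article does not rule out baseline pain. The primary covariate list is introduced as inclusive, and the secondary sentence promises a similar approach with appropriate models. A sympathetic reader could take this to mean that each outcome gets its own relevant baseline, as the OSS does. The interim-OSS element points the same way: its natural counterpart in a pain model is interim pain, so some translation between outcomes must be intended. The article also defers detail to a statistical analysis plan, which is not shown here.

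Much of this stands. A reader might infer that the protocol definitely excludes baseline pain; an open list does not support that. It does not remove the point, however. The open list belongs to a model for the OSS, and the secondary sentence does not stay silent on covariates but says they are the same ones. If the intention is each outcome's own baseline, the sentence does not express it.

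It is also fair to say that the primary model itself names only the pre-fracture OSS, although a post-injury OSS is collected. The design seems to favour pre-injury status, and no pre-injury pain score is described. This limits the likely gain. It is no reason to omit the only pain baseline available.

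**Conclusion.** The point holds as a low-cost improvement to two secondary outcomes. Followed as written, the secondary sentence leaves pain VAS and PROMIS without adjustment for their own baselines. The precision forgone is about 1% to 16% of residual variance, or about 1% to 19% in equivalent participants. That range rests wholly on an assumed partial correlation of 0.1 to 0.4, and the truth may lie near the bottom.

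Three stronger readings are not supported:

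- **Bias.** A reader might infer that the pain comparisons would be biased. Leaving out a baseline covariate does not bias a randomised comparison; only precision and correction for chance imbalance are affected.
- **A stated error in VAS points.** A reader might want the effect of a given baseline imbalance on the pain estimate. That needs a regression slope and standard deviations, which the documents do not give, and a correlation cannot stand in for a slope.
- **All secondary outcomes.** Range of motion has no baseline in the schedule, and OSS at 6 and 12 months already has pre-fracture OSS. EQ-5D-5L is not named in the secondary sentence. The primary analysis is untouched.

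**What to change.** In the Secondary analyses section, add that pain VAS and PROMIS pain interference will each be adjusted for its own baseline value, with the other primary-model covariates retained. If the statistical analysis plan already says this, the two documents only need to be brought into line.

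The cost is one sentence and one extra parameter in each pain model. No new data are needed. The handling of missing baseline pain scores should be stated with it, so that adding the covariate does not remove participants from the analysis. Treatment is known to the analysing statisticians, so the choice should be fixed before outcome data are examined.

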### Interim analyses {21b}

There are no planned interim analyses for the trial and no formal stopping guidelines in relation to the outcomes of the trial. There was an internal pilot phase, where recruitment and retention aims were assessed in line with the feasibility of the trial — the funder approved the continuation of the trial past the pilot phase. No comparison of the primary outcome, or any other formal analysis, was undertaken as part of the pilot phase.

### Additional analyses {20b)

Sensitivity analyses will be undertaken to explore the effect of surgeon expertise in the RSA vs HA comparison. Details of the SWAT analysis will be included within the publication of the results [36].

### Methods in analysis to handle protocol non-adherence and any statistical methods to handle missing data {20c}

The primary analysis models will be repeated using data sets where the primary outcome (OSS at 24 months) and any of the model covariates that are missing have been imputed using appropriate imputation methods.

Additionally, analyses will be undertaken to explore the effect of non-compliance, where participants do not receive the treatment to which they were randomised—such as using a complier average causal effects (CACE) analysis.

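### Missing baseline covariates are imputed only in a repeat of the primary models, so as written the primary run would by default drop participants whose OSS was observed

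*Protocol article*

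**What the plan says.** Under Primary analyses, the protocol article states that "The difference in OSS at 24 months will be compared between the arms of the trials using mixed effects models". The model adjusts for "relevant baseline characteristics, including pre-fracture OSS, baseline grip strength, and presence of an associated dislocation (if applicable") and for a dummy marking the change in allocation ratio. Repeated OSS values within a participant are linked by a covariance structure.

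Missing data are dealt with under {20c}. The primary models are to be run a second time on data sets in which a missing 24-month OSS is filled in. The same step extends to covariates, in that "any of the model covariates that are missing have been imputed using appropriate imputation methods". Imputation of covariates is therefore tied to a second run of the models, together with imputation of the outcome.

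The general statement under {20a} is that "All analyses will be undertaken using the principle of intention-to-treat, where participants are analysed as randomised" and that "Analysis will be undertaken using Stata v17 (or later"). No section gives a separate rule, such as a mean fill or a missing indicator, for a baseline covariate that is missing in the primary run.

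**The concern.** Two kinds of missing data are treated as one. A missing 24-month OSS cannot be recovered without assumptions, and a likelihood-based mixed model already uses whatever other follow-up scores that participant gave. Imputing the outcome belongs in a sensitivity analysis. A missing baseline covariate differs in two ways. The mixed model has no place for it, and standard fitting, including in Stata, leaves out every record that lacks it. A baseline value is constant within a participant, so all of that participant's OSS records go. Someone with OSS at 6, 12 and 24 months but no dynamometer reading would contribute nothing to the headline estimate.

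Some missingness is plausible. Grip strength needs a device and a physical test, and pre-fracture OSS is a recalled score collected after the injury. The article foresees missing covariates, since {20c} provides for imputing them. At stake is outcome data already collected, lost for want of a variable that serves only to adjust the comparison.

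**Working it through.** **Inputs from the article (Sample size {14}).** SD 12; two-sided 5%; 90% power; difference of 5 points for RSA v HA and 6 points for each surgical arm v NS; 320 evaluable; 15% attrition; target 380 (152/152/76).

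**Assumed input.** The share *m* of participants with observed OSS but a missing covariate is not given. I use 2%, 5% and 10%.

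**Step 1: reproduce the plan's figures.** With (1.960 + 1.282)² = 10.51:
- RSA v HA: n per arm = 2 × 12² × 10.51 / 5² = 121.1, so 122.
- Surgical arm v NS at 2:1: n in NS = 12² × (1 + 1/2) × 10.51 / 6² = 63.1, or 64 with the t-distribution. The surgical arms are then 128 each.
- Total: 128 + 128 + 64 = 320, as stated.
- Attrition: 320 / 0.85 = 376.5, so 377, close to the stated 380. In the other direction, 380 × 0.85 = 323, which is 3 more than 320.

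**Step 2: remove participants with a missing covariate.** Each arm size is multiplied by (1 − *m*), so the standard error is multiplied by 1/√(1 − *m*). With nothing missing, it is 12 × √(1/128 + 1/128) = 1.50 for RSA v HA and 12 × √(1/128 + 1/64) = 1.84 for a surgical arm v NS. Power is from the non-central t-distribution, two-sample and unadjusted.

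| *m* | Left of 320 | SE multiplier | RSA v HA (128/128, 5 points) | Surgical arm v NS (128/64, 6 points) |
|---|---|---|---|---|
| 0% | 320 | 1.000 | 91.3% | 90.1% |
| 2% | 313.6 | 1.010 | 90.8% | 89.6% |
| 5% | 304 | 1.026 | 89.9% | 88.6% |
| 10% | 288 | 1.054 | 88.3% | 86.9% |

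**Step 3: check the slack.** If *m* is 1%, 323 × 0.99 = 319.8. A missing-covariate rate of about 1% therefore uses up the margin between 323 and 320.

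**Step 4: allow for adjustment.** If the covariates jointly correlate *r* with 24-month OSS, adjustment multiplies the residual variance by about (1 − *r*²), while exclusion multiplies the variance of the estimate by 1/(1 − *m*). The two cancel when *r*² = *m*: *r* = √0.10 = 0.32 for 10% and √0.05 = 0.22 for 5%. The article gives no value for *r*, so this only marks where absolute power would be restored.

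**The case against.** **The exclusion is inferred.** The article never says that the primary run uses complete cases, and it defers detail to an analysis plan not shown here, which could contain a rule. This stands as a limit. But the article is not simply silent: it assigns covariate imputation to the repeat, which makes sense only if the first run does not impute.

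**The repeat restores those lost.** It does, and it would show whether their exclusion matters. The headline estimate would still come from the smaller set.

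**The loss is small and may be offset.** At 2% to 5% missing, power falls by about 0.5 to 1.5 points, and a modest correlation with the outcome would make that up. This stands as to size. However, the gain from adjustment is available whether or not these participants are kept, so it is no reason to drop them.

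**Few covariates are exposed.** The allocation-ratio dummy is known for everyone, and dislocation status bears on which allocation sequence is used, so it should rarely be missing. That leaves mainly grip strength and pre-fracture OSS, both scheduled before randomisation.

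**A stronger reading that fails.** A reader might infer that the exclusion breaks the intention-to-treat commitment. The article explains that principle as one "where participants are analysed as randomised, regardless of what treatment they received". This concerns assigned against received treatment and does not promise that every record enters the model.

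**Conclusion.** The point holds as a modest, nearly free improvement. As written, covariate imputation sits in a repeat analysis, nothing covers the primary run, and the default behaviour of the model is to discard observed OSS data from participants lacking a baseline covariate.

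The size rests on an assumed missing rate of 2% to 10% and on unadjusted power at the original 2:2:1 arm sizes; the true rate may be lower. Within that range the loss is at most 3.0 points for RSA v HA (91.3 − 88.3) and 3.2 points for a surgical arm v NS (90.1 − 86.9).

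Two further inferences are not supported. One is bias between arms: the covariates are scheduled before randomisation, so dropping participants who lack them does not by itself unbalance the comparison. The other is to blame this issue for any shortfall in the NS comparisons after the change to 1:1:1. That would be a matter of dislocation frequency and allocation, and the article does not give the arm sizes that resulted from a change made partway through recruitment.

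**What to change.** Add one sentence under Primary analyses or {20c}, and carry it into the statistical analysis plan. In the primary models, missing baseline covariates are filled by a pre-specified rule that uses neither allocation nor outcome: for example, the overall mean for continuous covariates and a missing-indicator category for categorical ones. Every participant in the relevant comparison with at least one post-randomisation OSS is then included. Because these covariates precede randomisation, such a fill is valid for the treatment comparison.

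Keep multiple imputation of the outcome as the sensitivity analysis, and report how many participants had each covariate filled, by arm. The cost is one sentence and a few lines of code. No new data are needed, and the rule can be set before analysis.
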